## **A pilot study to assess the effects of using FES or AFO as an assistive mobility device for a period of 12 weeks by people with MS with foot drop**

This research will be conducted as two distinct studies. Study one will investigate, in people with Multiple Sclerosis (pwMS), the effects of 12 weeks use of functional electrical stimulation (FES) on walking performance. The second study will investigate, in pwMS, the effects of 12 weeks use of an ankle foot orthosis (AFO) on walking performance. Each study will be conducted as a within-subject repeated measures pre-post comparison trial. Each study will follow the same protocol.

### **Identification and approach of potential participants**

People with MS who are identified by their physiotherapist as eligible candidates for the use of FES or AFO as part of their routine clinical care will be invited to participate in these studies. Participants will be recruited into either study one (FES) or study two (AFO) according to the clinical decision of which assistive device they are best suited to be prescribed. Two recruitment packs have been produced; one for potential FES study participants and one for potential AFO participants. Potential participants will be supplied with an information pack for the relevant study by their physiotherapist. The information pack will include an invitation letter, participant information sheet and a transfer of contact details (TCD) form.

If the patient is interested in finding out more about the study they are required to complete and sign the TCD form to agree to the clinician forwarding their contact details on to the research team at Queen Margaret University. Once the principal investigator (PI) receives the TCD form they will contact the potential participant. The potential participant will have the opportunity to ask questions about the study at this point.

If the potential participant wants to take part in the study, arrangements will be made (including transport if required) for them to visit Queen Margaret University on 4 occasions over a 16 week period. At their first assessment participants will again have the opportunity to ask any further questions before being asked to complete and sign a consent form.

### **Inclusion/Exclusion Criteria**

People with Multiple Sclerosis, aged between 18 and 70 years of age, who are referred to their physiotherapist to receive AFO or FES to combat foot drop will be considered for these studies. Participants who cannot walk without a walking stick or walking frame will be excluded from this study.

Patients who are pregnant or breast feeding will be excluded from the study. If participants experience a relapse during their involvement in the study they will be excluded from further participation. Participants who have cardiac or respiratory disease will also be excluded from the study. If the patient is concurrently participating in any other physiological research projects they will not be accepted into this study.

### **Interventions - Assistive Devices**

#### **Function Electrical Stimulation**

FES will be administered using the Odstock Dropped Foot Stimulator (ODFS III, Salisbury, Wiltshire, UK). The device will have been fitted to the patient as part of their routine care by their physiotherapist, who is

qualified to fit the stimulator units. Stimulation parameters of the stimulus will be adjusted to suit each participant. The electrode placement and the device settings will be noted and passed to the PI for use in this study.

#### **Ankle Foot Orthosis**

The AFO will be prescribed to the participant by their physiotherapist on an individual basis and fitted as part of their routine clinical care. Therefore different AFO's will be included in the study. However all AFO's will perform the intended function of reducing foot drop.

#### **Timescale**

Participants will be involved in this study for 16 weeks during which time we will request that they make 4 visits to the gait lab at Queen Margaret University. Each testing session will take approximately 2 hours to complete.

#### **Protocol**

Participants will attend their first assessment before they receive their assistive device. During their first assessment they will only be tested walking without assistance. Once they receive their appropriately prescribed assistive device they will be tested again (with and without their device). Participant will use the device habitually on a day to day basis to assist their walking. They will then be tested on a further two occasions separated by a period of 6 weeks.

Each participant will be tested at the same time of day (+/- 1 hour) each time they are tested.

#### **Testing Sessions**

Participants will be asked to report to the main reception at Queen Margaret University and ask for the PI. Participants will be asked to wait at the main reception until a member of the research team collect them and take them to the gait lab in a wheelchair.

Prior to each testing session the computerised 3 dimensional motion analysis system (Vicon) will be calibrated using a standardised method according to the Vicon manual.

The study will be fully explained to the participant at the start of the assessment session 1. They will be shown the equipment and the laboratory and have the opportunity to ask questions. Once all questions have been satisfied and the participant is happy to proceed they will be asked to complete and sign a consent form before commencing testing.

Participants will carry out eight 6-7-metre walks without their assistive device and eight 6-7-metre walks with their assistive device while their gait is digitally recorded using Vicon three dimensional motion analysis (Vicon, Nexus, Oxford, UK). Participants will be asked to walk how they would do normally at their preferred walking speed.

Participants will also be asked to carry out one timed 10 metre walk without their assistive device and one timed 10 metre walk with their assistive device (Paltamaa *et al.*, 2005). In addition participants will be asked to carry out two 2-minute walk tests, one with and one without their assistive device.

At each testing time point participants will be asked to complete four short questionnaires. They will also be given an activPAL physical activity monitor to take away with them at the end of each testing session to wear for a week.

## Procedures

### Physical Measurements

Anthropometric and information (height and weight, knee width, ankle width and leg length) will be collected at each visit for the calculation of the ankle, knee and hip joint centres by the motion analysis software ('Plug in Gait').

Body composition assessment by multi-frequency, bioelectrical impedance analysis (BIA) will also be carried out at the beginning of each testing session using a Maltron Bioscan 920-2. While the participant is lying down at rest we attach electrodes to their foot, ankle, hip, shoulder, wrist and hand (on their left hand side). An electrical impulse is passed between the electrodes (which the participant does not feel). The BIA analyser records the time taken for the electrical impulse to travel between each electrode and uses these results to calculate body composition.

### Gait Analysis

Participants will have 14mm reflective sphere makers, which are visible to the infra red cameras, placed on their lower limbs and pelvis, using skin friendly hypoallergenic double sided tape. They will also be asked to wear black cycling shorts (provided) so that markers can be attached directly to their hips.

### 10m Walking Test

Participants will be asked to walk in a straight line at their preferred walking speed (PWS) through the start line, straight towards the end of the walkway. The time to complete the 10m walking test will be recorded manually using a stop watch. The clock will be started and stopped when a foot either falls on or passes over the start and finish line respectively. Seconds will be recorded to two decimal places.

### 2 Minute Walking Test

Two 2-minute walk tests will be conducted at each testing session. Participants will be given a 15 minute rest in between the two 2-minute walks to ensure they start both walks in the same physiologically rested state. Participants will be asked to walk continuously around a 16m elliptical course for 2 minutes at their preferred walking speed. The distance travelled will be recorded by recording split times each time they complete a lap and by marking the point on the course they reach in 2 minutes. If they need to stop they can stand or lean against a wall and then continue. If they need to stop and sit down the test will be terminated.

Participants will be asked to rate their perceived exertion (RPE), according to the Borg category rating scale (Borg, 1970) in the middle and at the end of 2-minute walk test.

Participants will be asked to mark on a 10cm line labelled from 'no fatigue' to 'severe fatigue' (Johnson, 2005), how fatigued they feel immediately before and after the 2 minute walk test.

## Questionnaires

Participants will be asked to complete the following four questionnaires at each assessment. After the first assessment the four questionnaires will be posted out to the participants a week prior to their next assessment. They will be asked to complete the questionnaires again and send them back to Queen Margaret University in a pre paid envelope or bring them in with them to the next assessment.

Fatigue will be assessed by:

- Fatigue Severity Scale (Krupp *et al.*, 1989)

Activity of Daily Living will be assessed by the:

- 12 Item MS Walking Scale (Hobart *et al.*, 2003)

Quality of Life will be assessed using:

- Leeds MS Quality of Life Questionnaire (Ford *et al.*, 2001)
- MS Impact Score 29 (Hobart *et al.*, 2001)

## Physical Activity Monitoring

Physical activity levels will be measured using the activpal™ activity monitor. This is a small accelerometer device (size 53 x 35 x 7 mm; weight 20g) which attaches directly to the skin of the front of the thigh using activpal adhesive stickers (activstickies).

Participants will be asked to wear the device 24 hours a day for 7 days after each testing sessions.

## Statistics

### Sample Size Calculation

Both the FES and the AFO studies are pilot studies and with the aim being to help determine the factors which will inform the sample size (e.g. variance) for the main study and to assess the feasibility of steps that need to be taken for a future study such as recruitment and retention rates (Thabane *et al.*, 2010).

A sample size of 6 will have 80% power to detect an effect size of 1.435 using a paired t-test with a 0.050 two-sided significance level. Taking into account data loss and attrition this was inflated to 12 participants.

### Analysis of Data

Following checks for normality the gait kinematic data will be analysed using paired t-tests. Where appropriate; parametric tests will be used to evaluate the effect of the respective interventions on the primary outcome measure of gait kinematics. A similar statistical approach will be applied to the times walking performance and the physical activity data. If parametric assumptions are not met appropriate non parametric tests (Wilcoxon test) will be employed.

In all analyses a significance level of  $p < 0.05$  will be regarded as statistically significant.

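### The primary outcome is a whole domain (gait kinematics) with no variable or pair of conditions named, and every test counts as significant at an unadjusted 0.05

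*Protocol*

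**What the plan says.** The opening paragraph of the protocol says that study one will investigate "the effects of 12 weeks use of functional electrical stimulation (FES) on walking performance". It gives study two, on the ankle foot orthosis (AFO), the parallel aim, and describes both as within-subject pre-post comparisons.

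Under Analysis of Data, the gait kinematic data go to paired t-tests, with Wilcoxon as the fallback, and "parametric tests will be used to evaluate the effect of the respective interventions on the primary outcome measure of gait kinematics". Timed walking and activity are handled next: "A similar statistical approach will be applied to the times walking performance and the physical activity data". The section closes with one rule for everything: "In all analyses a significance level of" p < 0.05 counts as statistically significant. No order of testing and no adjustment is given.

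Sample Size Calculation states the pilot's "aim being to help determine the factors which will inform the sample size (e.g. variance) for the main study", together with feasibility, recruitment and retention. It then says "A sample size of 6 will have 80% power to detect an effect size of 1.435 using a paired t-test" at a two-sided 0.05 level, and raises 6 to 12 for data loss and attrition. It names no outcome, raw difference, standard deviation or pair of conditions.

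The Protocol and Testing Sessions sections give one condition at visit 1 (no device) and two at each of visits 2, 3 and 4 (with and without device). Physical Measurements shows that the motion analysis covers at least three joints, since measurements are taken "for the calculation of the ankle, knee and hip joint centres by the motion analysis software".

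**The concern.** A primary outcome should lead to one identifiable test, or to a stated set of tests with a rule for combining them. Here a domain is called primary, and both the variable and the comparison are left open.

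The choice of pair is also a choice of question. With versus without the device at one visit measures the immediate assistive effect. Unassisted walking at visit 1 versus visit 4 measures a carry-over effect of 12 weeks' use. Visit 1 without the device versus visit 4 with it mixes the two.

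Two things are at stake. First, with every comparison judged at 0.05, any one of several kinematic results could be reported as a significant primary finding. Second, the pilot is meant to supply a variance for the main study, and the protocol does not say which variable and which within-person difference that variance belongs to.

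**Working it through.** **1. The plan's own figure.** Inputs from Sample Size Calculation: n = 6 pairs, standardised effect d = 1.435, two-sided α = 0.05. Power is P(|T| > t(1−α/2, n−1)), where T is noncentral t with n−1 degrees of freedom and noncentrality d√n.
- Noncentrality: 1.435 × √6 = 3.515.
- Power: 80.02%, so the stated 80% reproduces.
- If all 12 complete: 1.435 × √12 = 4.971, and power is 99.4%.

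**2. Number of possible comparisons.** Conditions: 1 + 2 + 2 + 2 = 7. Possible pairs per variable: 7 × 6 / 2 = 21. The protocol does not say how many of these will be tested, or on how many variables.

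**3. Chance of at least one false-positive primary result.** Assumptions, not in the protocol: one variable per joint, three joints, between-joint correlation 0 to 0.8, no true effect, and equal variance and equal correlation among a participant's conditions. For k independent tests the chance is 1 − 0.95^k. Contrasts that share a condition are not independent, so that formula overstates the chance. The last column comes from simulating paired t-tests with the shared conditions kept.

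| Contrasts per variable | Tests k | 1 − 0.95^k | Simulated, correlation 0.8 down to 0 |
|---|---|---|---|
| 1 | 3 | 14.3% | about 11–14% |
| 2 | 6 | 26.5% | about 18–25% |
| 7 | 21 | 65.9% | about 47–60% |

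The seven contrasts are with versus without device at visits 2, 3 and 4; unassisted visit 1 versus unassisted visits 2, 3 and 4; and visit 1 without versus visit 4 with device. The simulated figures move by about one percentage point between 6 and 12 participants.

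**4. Power if several tests were kept with Bonferroni.** Same power formula, with α replaced by 0.05/k and d = 1.435.

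| Tests k | Level | Power, n = 6 | Power, n = 12 | Completers for 80% |
|---|---|---|---|---|
| 1 | 0.05 | 80% | 99% | 6 |
| 3 | 0.0167 | 55% | 97% | 9 |
| 6 | 0.0083 | 39% | 93% | 10 |
| 10 | 0.005 | 29% | 89% | 11 |

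**The case against.** The strongest reply is that this is a 12-person pilot whose stated aim is variance and feasibility. Significance testing is secondary to that aim, multiplicity control in such a study is partly a matter of preference, and detail may sit in a statistical analysis plan that is not shown. This lowers the severity. It does not remove the point: the protocol itself names a primary outcome, makes a power claim and fixes a significance rule for all analyses, and identifying the primary variable and contrast is the protocol's job.

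The pre-post wording in the opening paragraph does narrow the intended comparison. It does not settle whether the later measurement is with or without the device.

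A reader might infer several stronger things that the protocol does not support:
- **That a chance significant primary result is likely.** The test count is not stated. With one or two contrasts on three variables the chance is well below one half. The independence formula gives 66% for 21 tests, but that ignores the shared conditions.
- **That the 80% power belongs to no defined test.** The test type, sidedness, level, sample size and standardised effect are all given ("using a paired t-test with a 0.050 two-sided significance level"), and paired t-tests on kinematic data are planned. Only the variable and the pair of conditions are missing.
- **That power collapses under adjustment.** It does at 6 completers. At the planned 12 the loss is small. The protocol proposes no such adjustment in any case.
- **That the primary outcome contradicts the aim.** Walking performance can be read to include gait. Analysis of Data does list timed walking performance separately, so the link should be stated, but this is a secondary matter.
- **That a significant kinematic result would decide the main study.** Nothing in the protocol makes progression depend on it.

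**Conclusion.** The point holds in a limited form. The primary outcome is a domain, with no variable and no pair of conditions fixed among seven, and every test is judged at an unadjusted 0.05. The false-positive rate on the primary outcome is above 5% for any set of more than one test: about 11–14%, 18–25% or 47–60% for one, two or seven contrasts on three variables. These figures rest on the assumed number of variables and contrasts and the assumed correlations, none of which the protocol gives.

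The 80% power is correct as arithmetic but is not attached to a named variable or contrast. Severity is moderate, given the pilot purpose, and the remedy is a cheap improvement.

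**What to change.** In Analysis of Data, name one primary kinematic variable and one primary contrast for each study, chosen to answer the 12-week question in the opening paragraph. One example is peak swing-phase ankle dorsiflexion, compared between a stated pair of conditions that includes the 12-week visit. The exact choice is the investigators'.

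Then make three matching edits:
- In Sample Size Calculation, say that the effect size of 1.435 and the 80% power refer to that variable and contrast.
- In the opening paragraph, say how the chosen variable relates to walking performance.
- Report all other kinematic, timed-walk and activity comparisons as exploratory, as estimates with 95% confidence intervals and no claim of significance.

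The cost is wording, and fewer results can be called significant. No sample size change is needed: one named test at 0.05 keeps 80% power with 6 completers and 99% with 12. The pilot also gains a defined within-person variance to pass to the main study.

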## Ethical Opinion

This study has been reviewed and approved by the NHS Lothian ethics and management committee. In addition the Queen Margaret University research ethics committee have approved this study.

